**Methods:** We will employ cluster-randomized controlled design. Through elimination by factors such as proximity to circumcising communities, multi-ethnic urban populations, and geographical proximity to each other, 45 administration Locations in Nyanza Province have been selected and randomized into IPC implemented alone, DSO implemented alone, IPC and DSO implemented together and control. Under IPC, we will develop a Toolkit for Addressing Barriers and Facilitators to VMMC with messages that address barriers to and reinforce facilitators of VMMC, and engage behavioral counselors to deliver intervention massages that are custom-made to address participants’ specific issues; Under DSO, selected facilities, days and hours will be set aside to serve only men aged ≥25 years; these sites will be served by older, male providers only; Under Combined IPC and DSO, the effect of both interventions implemented together will be examined; and in the Control locations, no intervention will be implemented. Altogether, 4,932 men aged 25-39 years are expected to take up VMMC during the study period, which will take up to nine months.

For aim 2, we will collect blood samples from bleeding vessels of an estimated 700 men whose HIV status is unknown, and perform unlinked test for HIV at the KEMRI/CDC HIV Laboratory in Kisumu. For aim 3, we propose to extract from our procurement, stores and accounts records expenditures for demand creation and service delivery.

To augment this study, we will nest a sub-study (sub-study 4) in all the 45 study Locations and enroll approximately 720 men who are in stable sexual relationships, together with their partners, for post circumcision follow up visits to monitor the impact of involving female partners on time to resumption of sex post-surgery.

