2. Separating eligible from ineligible Locations: To ensure the populations in participating Locations are as homogenous as possible in terms of ethnicity (which defines circumcising and non-circumcising communities), we spread the map on a flat surface and systematically identified and excluded 37 Locations: 34 bordering traditionally circumcising communities in Kuria, Gucha, Central Kisii, Nandi, Vihiga, Butere-Mumias and Busia districts, and 3 within cosmopolitan Kisumu city where mixed ethnic communities live. In addition, we excluded 5 Locations in the islands due to poor access. Consequently, we remained with 122 eligible Locations to select from (Fig 2: Map 2).
3. Selecting participating Locations: Of the remaining 122 eligible Locations, we randomly selected the starting point and went through the process of systematically selecting each Location and excluding all the contiguous ones until we identified the maximum possible Locations that did not share a boundary. This exercise was done repeatedly by randomly selecting different Locations as the starting point and seeing how many Locations we ended up with. The goal was to select the highest number while ensuring none is proximal to each other. Based on these selection criteria, 45 was the maximum number of Locations that could be included in the study (Fig. 2: Map 3).
4. Random assignment of participating Locations: The names of the 45 Locations were compiled and submitted to the study Biostatisticians (FO & VS) for randomization.The names were entered into Stata V12 statistical package and a randomization schedule produced using the random-number generator. Using simple randomization to allocate clusters, roughly equal number of Locations (11-12 per arm) was allocated to each of the four study arms (Fig 2: Map 4).

A summary of the steps and the number of locations are shown in *Table 1* below while randomization and distribution of allocation to the study arms by districts are shown in Tables 2 and 3.

**Table 1:** Summary of Selected Study Locations

| **Total Locations in *Luo* Nyanza Province** | 233 |
| --- | --- |
| Locations where IRDO is providing VMMC services | 194 |
| Locations excluded because of an ongoing pilot demand creation study | 30 |
| Locations excluded because they border traditionally-circumcising communities | 34 |
| Locations excluded because of having a multi-ethnic population | 3 |
| Locations excluded because of poor accessibility (Islands) | 5 |

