# PHASE 1: HOUSEHOLD ENUMERATION

To ascertain the size of eligible population (uncircumcised men aged 25-39 years), we will conduct complete household listing in all selected villages and enumerate male members in each household aged 25-39 years (Appendix 1: Household Enumeration Form). During this exercise, we shall physically visit all homes in the study villages and assign a unique identification number to every household (HIN ), which will be preceded by a pre-assigned study Location and village codes (e.g., KAW/KOD/1234 for Kawino Location and Kodongo village and Household number 1234). Enumeration shall be through home visits ONLY and not by any other means. The unique HIN assigned during the enumeration will be entered on Excel database and households with men aged 25-39 years will be sorted out and put on a separate list. The names and identifying information shall be kept separately from the main database (in a locked, password protected file) and will not be accessible to the person(s) working on the analysis.

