At this visit we will also collect names and telephone numbers (where known/available) of men aged 25-39 years to help us prepare a list of those to be reached by the intervention and contact them by phone or home visit to make appointments for baseline survey. We will also collect locator information of households with men aged 25-39 years, to guide the study staff who will return later for enrolment visit. At the end of the household enumeration, the data manager will prepare a complete listing of potentially eligible men in an excel sheet and the RAs will visit everyone in this list. During enrollment the RA will administer consent, assign Participant Unique ID (see pg xx), conduct baseline interview and verify the MC status of consented participants.

The list will be used to create a log of eligible men in each village. Determining the number of households with eligible men will help in knowing the denominator and in planning for recruitment. Once this information is obtained, we will use it to start planning for Phase 3 of the study (Conducting Rapid Formative Study). Phase 2 (Establishing Baseline VMMC Prevalence and Proportion of Eligible Men) of the study, described here below, will be implemented concurrently with Phase 1. In addition, we have drafted the tool [to be known as *VMMC Demand Creation Tool*] which will be used for demand creation in IPC and IPC+DSO Locations. Before being used, this tool will be updated with information collected from the formative phase of the study and submitted to the two IRBs for approval prior to implementation. We have attached herewith the draft version for initial review (Appendix 16: VMMC Demand Creation Tool). All eligible men in the selected villages will be approached to join the study.

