After assigning the participant unique ID number, the RA will conduct the baseline interview (Appendix 2B: 2 Questions for All Clients aged 25-39 yrs at Counseling), verify the MC status and inform participants of their intervention arm and deliver the intervention if participant is available (if not, another visit will be made at a later date to deliver the intervention). During the interview, we will document participants’ circumcision status from verbal report. After the interview, participants who consented to physical examination will be asked to choose where this can be performed. The identified location shall be acceptable to both the participant and RA. Physical verification will be done to minimize mis-reporting and/or misclassification, especially by those who are partially circumcised or who were born with short foreskins. Circumcision status will be recorded as fully circumcised (no foreskin), partially circumcised (foreskin is past corona sulcus but covers less than one half of the glans, in a flaccid state), and fully uncircumcised (foreskin covers half or more of the glans, in a flaccid state) and recorded on Appendix 2B.

We estimate that consenting will take about 30 minutes, the interview will take about 45 minutes, penile inspection will take about 5 minutes, altogether approximately 1½ hours. Where the participant is ready for the intervention, the RA will proceed to provide the intervention given that the participant will have consented to it. The delivery of the IPC and IPC/DSO intervention will take additional 1 hour while in DSO-only Locations; the process will take additional 30 minutes. Where a participant does not have time, another visit will be made (see Phase 4 below).

Details of participants enrolled in the study will be entered into an excel Master Log (Appendix 14) which will contain all participant details; 3 names, ID number, age, location, village, telephone number of the participants or of close friend and date of enrollment.

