**Inclusion/Exclusion Criteria for Baseline Phase**

Inclusion:

- Aged 25 – 39 years
- Resident of the study village - has been living in the physical structure identified during the enumeration and who has been eating together in the same household.
- Intends to continue living in the village for the next 9 months (which is the estimated duration of data collection).
- Gives written consent to participate in the study and the interventions.

Exclusion:

- Outside the age range of 25-39 years
- Non-resident of study villages
- Intends to relocate from the study village within the next 9 months
- Declines *to consent to participate in the study or the interventions*

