Moving on to the facilitators for VMMC, the RA will then pick each benefit/facilitator mentioned by the person/family members and reiterate their importance, ensuring sufficient and correct information is given. To conclude, the RA will encourage the men to seek VMMC and ask them to urge their family members and friends to also go for circumcision. The RA will leave behind a referral coupon (Appendix 15) indicating sites where VMMC is being offered in the neighborhood and contact information of team leaders in case of questions. Copies of *Appendix 17: ‘All You Need to Know About VMMC’ booklet* will be left with each person/family reached, for ongoing reference and to share with others.

While different RAs will reach out to potential participants to create demand for VMMC and make referrals to service provision sites, the effectiveness of each cadre of RA (behavioral counselors, CHWs, teachers, VMMC clients, etc) will be assessed through the number of referral coupons surrendered at the VMMC clinic after circumcision. Those who have forgotten/lost their referral coupons will be asked for the serial number of their referral coupon, which will be confirmed from the Tracking Log (Appendix 3A) and matched with the RA assigned to the respective Location and village.

**Study Arm 2: Designated service outlets (DSO) intervention** One of the concerns older men have expressed about going for VMMC services at current facilities is the fact that they are made to queue with age mates of their children.^23^ They find this embarrassing given VMMC is a private affair and one that touches on sexuality, an often taboo subject between parent and child in many African households.^26^ Also, because VMMC has been largely marketed as an HIV and STI prevention strategy, older men believe young people may perceive them as going for circumcision because they are promiscuous. To make older men feel comfortable going for VMMC, we plan to set up DSOs to serve men aged ≥25 years, exclusively.

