Recruitment Approach and Delivery of the DSO Intervention: If not done at enrollment visit, the RAs shall visit every household with eligible men (uncircumcised, age 25-39 years) in Arm 2 to inform them about the availability of DSO sites in their neighborhoods. For participants in this arm, the RAs will describe DSOs as sites where services are offered exclusively to men aged ≥25 years. These will include designated health facilities (including private facilities) and designated days of the week in selected health facilities. They will also include providing services in the evenings and weekends, and through special mobile services targeting older men only. In all the DSO sites, participants will be served by male staff in the same age bracket.

Potential participants will also be informed that at DSO sites we will strive to shorten the waiting time to no more than three hours. A floating circumcision team will be called upon whenever there is a surge of participants, and we shall establish a system of rebooking participants who arrive late, or as soon as it is apparent that surgery cannot be done the same day. There will also be information that all other VMMC sites continue to serve all men regardless of age (i.e., including older men) while DSO sites will only serve men aged ≥25 years.

After describing the characteristics of DSO sites, the RA will share - both verbally and through a flyer (Appendix 18: DSO Sites and Location Information) - information on where to find DSO sites in the respective Location. If there are questions from participants, they will respond using: *All You Need to Know About VMMC* booklet (Appendix 17), the same way current recruiters do.

To monitor which questions are asked and how they are responded to, we have developed a monitoring tool (Appendix 19: Monitoring Form for Demand Creation Strategies) to document demand creation activities, and have included questions asked by participants. Staff will be trained on how to pass sufficient information using Appendix 17 without going into details contained in IPC. The monitoring tool will enable us to identify DSO and Control participants who may have received information that puts them close to IPC recipients. In addition, different group of RAs will be trained only on the intervention they will deliver, thus minimizing the chance that DSO RAs will have sufficient information on IPC to conflate the two during intervention delivery.

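### Every Location's arm is fixed before men are listed, consented and screened, and no one who enrols them is masked, so the enrolled denominator can differ by arm.

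*Protocol*

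**What the plan says.** **Allocation comes first.** The Abstract states that "45 administration Locations in Nyanza Province have been selected and randomized into IPC implemented alone" and the other arms. The cluster-selection steps report it as done: "Using simple randomization to allocate clusters, roughly equal number of Locations (11-12 per arm) was allocated to each of the four study arms". Tables 2 and 3 print the arm of every Location.

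**Listing and enrolment follow.** In Phase 1, "we will conduct complete household listing in all selected villages and enumerate male members in each household aged 25-39 years", and "All eligible men in the selected villages will be approached to join the study". In Phase 3 the RA obtains consent in the household, enrols and interviews the man, and must then "verify the MC status and inform participants of their intervention arm and deliver the intervention if participant is available". Phase 3 also allows extra time at that visit by arm: 1 hour for IPC and IPC/DSO, 30 minutes for DSO. Under Study Arm 4, control men get the booklet information at enrolment.

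**Entry involves judgement.** The baseline criteria include residence and consent to the study and the interventions, and they exclude a man who "Intends to relocate from the study village within the next 9 months".

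**Staffing.** The DSO section says that a "different group of RAs will be trained only on the intervention they will deliver". The IPC section says that "the effectiveness of each cadre of RA (behavioral counselors, CHWs, teachers, VMMC clients, etc) will be assessed through the number of referral coupons surrendered". Table 8 places household survey and baseline work in Phases 1 and 3, and recruiter training in Phase 4.

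**Analysis.** Data Analysis, Aim 1, compares the proportion circumcised in each intervention arm with control.

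**The concern.** Randomising Locations balances the men who live in them, in expectation. It does not balance the men who are enrolled from them if the person seeking consent knows the arm. As Phase 3 is written, the RA cannot carry out the visit without knowing it, because the same visit may end with arm-specific delivery.

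A man can drop out of the denominator by refusing, by being judged likely to move, or by not being judged resident. If reluctant men are lost a little more readily in intervention Locations than in control, uptake among the enrolled rises there with no intervention effect. Neither the GEE model nor the Bonferroni adjustment removes this. The plan's allowance for refusal in Sample size Determination only raises the number of men to contact; it does not deal with bias.

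**Working it through.** **Inputs from the protocol (Sample size Determination).** Uptake 30%, target 40%, 1,233 per arm, design effect 2.5, two-sided alpha 0.05/3 = 0.0167 (rounded there to 0.017), refusal 15%.

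**The plan's own figure.** The two-proportion formula with pooled variance and continuity correction, at alpha 0.017 and 80% power, gives 493 per arm for 30% v 40%. Then 493 × 2.5 = 1,232.5, i.e. 1,233. For 30% v 45% it gives 229 × 2.5 = 572.5, i.e. 573. Both stated figures reproduce, and this point does not affect them.

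**Rejection probability under no effect.** Effective n per arm = 1,233/2.5 = 493.2, and the critical z at 0.0167 two-sided is 2.394. With control at 0.30, apparent intervention uptake p, difference d = p − 0.30, pooled standard error s0 and unpooled standard error s1, the probability is approximately Φ((d − 2.394·s0)/s1). The other tail is negligible except at very small d, where it is included.

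**Scenario A: reluctant men are passed over (assumption).** True uptake is 30% in both arms. Control enrols 85% of all men. In the intervention arm 85% of would-be takers enrol, but a fraction r of non-takers does not. Apparent uptake p = 0.30×0.85 / (0.30×0.85 + 0.70×(1 − r)).

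| r | Overall non-enrolment | p | Spurious points | Rejection |
|---|---|---|---|---|
| 0.15 | 15.0% | 30.0% | 0 | 1.7% |
| 0.20 | 18.5% | 31.3% | 1.3 | 2.8% |
| 0.25 | 22.0% | 32.7% | 2.7 | 7.0% |
| 0.30 | 25.5% | 34.2% | 4.2 | 16.5% |
| 0.35 | 29.0% | 35.9% | 5.9 | 34% |

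For the last row, s0 = 0.02993 and s1 = 0.02987, so (0.0592 − 0.0717)/0.02987 = −0.42 and Φ = 0.34.

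**Scenario B: worst case (assumption).** Non-enrolment is 15% in both arms. In control it is unrelated to willingness; in the intervention arm it consists only of non-takers. Then p = 0.30/0.85 = 35.3%, which is 5.3 spurious points and about 27% rejection. If the non-enrolled would go at 10%, p = (0.30 − 0.15×0.10)/0.85 = 33.5% and rejection is about 11%.

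**Would a listed-men denominator repair it?** Count the non-enrolled as not circumcised.
- Scenario A: both arms give 0.30×0.85 = 25.5%, so the bias is removed.
- Scenario B: control gives 0.30×0.85 = 25.5% and intervention 0.353×0.85 = 30.0%. So 4.5 of the 5.3 points remain, with about 25% rejection at 1,233/0.85 ≈ 1,451 listed per arm. In the 10% variant, 28.5% v 25.5% leaves 3.0 of 3.5 points and about 11% rejection.

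Scenario A shows up as unequal enrolment by arm (15% v 18.5% to 29% not enrolled). Scenario B does not, because 85% enrol in both arms.

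**The case against.** The protocol has real safeguards. Listing is complete, every eligible man is to be approached, RAs return up to three times, and validation revisits bring in eligible men who were missed (Quality assurance of data entry). One consent covers all arms, and the man learns his arm only afterwards. Circumcision status has anatomical definitions and physical verification. All of this stands and lowers the risk. It blinds the man at consent, however, and not the RA who persuades him or judges his intention to stay.

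Three stronger readings are tempting, and the protocol does not support them.

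- *Enrolling staff are rewarded for uptake.* The coupon sentence compares cadres of RA, stands in the IPC section, and states no individual rating or incentive. It also uses a count, which passing over a reluctant man cannot raise.
- *Enrolling staff are separate teams by arm.* The sentence on separate training concerns keeping IPC content out of DSO delivery. Ethical Considerations requires enumerators and verifiers to be men aged 25-39, whereas IPC communicators may include female partners, and Table 8 trains recruiters after the baseline. These point to different people. Phase 3 points to the same person. The text does not settle it.
- *The bias will be about 5 points.* That figure assumes no selection at all in control. Refusers may be less willing in every arm, and shared selection largely cancels.

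It is also fair that sensitivity analyses may sit in an analysis plan that is not shown. Who enrols, and what they know at that moment, is fixed by the protocol.

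**Conclusion.** The point holds in this form: allocation precedes listing, consent and screening; no passage masks the enrolling RA; Phase 3 combines enrolment with arm disclosure and possible delivery, at odds with the order in Table 8; and men not enrolled leave the primary denominator. Selection needs only knowledge of the arm, not an incentive.

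The size cannot be derived from the protocol. Under the stated assumptions it runs from about 1 to 6 spurious points against a planned difference of 10, with false rejection of about 3% to 34% instead of 1.7%. The 35.3% v 30% case (27%) is a worst case. The change should be made before enrolment, because analysis can repair the bias only in part.

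**What to change.** 1. **Separate enrolment from delivery, in Table 8's order.** Have the baseline team complete eligibility, consent and verification for a whole Location, with the men entered in the Master Log, before that Location's arm is released to field staff. Delivery then falls at the later visit that Phases 3 and 4 already allow. Table 3 should not be in the baseline team's hands until then. Reconcile Phase 3, Phase 4 and Table 8 to say this. The cost is extra field time. Because the 3-month period for capturing circumcisions now starts at enrolment, its start must also be reconciled so that it is the same in all arms.

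2. **Make selection visible.** Report enrolled/listed and reasons for non-enrolment by arm, and log men added or removed at validation visits. Add a sensitivity analysis on all listed men not verified as circumcised at baseline, counting the non-enrolled as not circumcised. State its limits: it corrects the passing-over of reluctant men but not differences between arms in enrolling willing men; its denominator includes refusers whose status was never verified; and equal enrolment proportions do not rule out selection. The Phase 1 listing already supplies the denominator, so the cost is recording reasons for non-enrolment and some analysis wording.

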### Demand creation for all other ages

Because the study targets only older men, demand creation for younger men/boys will continue as part of program work. As such, routine recruitment activities will continue for all men in all Locations; these include distributing information, education and communication materials; conducting road shows and magnet theater events to promote VMMC services; carrying out one-on-one or small group face to face interactions with community members, asking those who have been circumcised to refer others; visiting social events to pass information and invite men for service; using radio to present information of VMMC; and so on.

##

